### Sample size

This study is designed as a superiority trial based on previous cohort series. According to power calculations finding a difference of 10 in %EWL with the assumptions of mean %EWL = 60 (standard deviation (SD) = 17) in the RYGB group, with alpha = 0.05, 50 patients in each group would be sufficient to reach the power of 80%. If a drop-out of 10% is taken into account, this would mean 55 patients per group. Power calculations were performed by simulation using the Mann-Whitney-Wilcoxon test (PASS v13.0, NCSS Inc., Kaysville, Utah, USA). Since there was a lack of published data on comparisons between these two operations at the time of designing the study, we decided to recruit 60 patients for both treatment groups in order to have sufficient statistical power regarding the primary end point (10% difference in %EWL at 2 years between the groups).

### Inclusion criteria

Inclusion criteria were:
Age >18 yearsBMI ≥35 kg/m^2^Eligible for gastric bypass surgery according to national treatment guidelinesWillingness to participate in this trial

### Exclusion criteria

Exclusion criteria were:
Anemia (hemoglobin <120 g/l)Pregnancy or lactationFor MRI/MRS imaging: metal objects in the body or claustrophobiaEndoscopic evidence of hiatal hernia, reflux esophagitis or Barret’s esophagusAny other condition that, in the opinion of the investigator, could create a hazard for the safety of the participant, endanger the study procedures or interfere with the interpretation of study resultsLack of consent

### Study sites and randomization

The trial is being carried out in two academic centers: HUH in collaboration with the University of Helsinki, and Oulu University Hospital (OUH). Both bariatric centers (HUH and OUH) are university hospitals that are tertiary referral bariatric centers with a catchment area of around one million people in Finland. Metabolic studies for patients in HUH are conducted by the Research Program for Clinical and Molecular Metabolism, University of Helsinki.

The trial is carried out according to the Consolidated Standards of Reporting Trials (CONSORT) statement. The trial schedule is shown in Fig. 1. Surgeons performing the intervention recruit eligible patients at a preoperative visit (study baseline) and randomize them according to protocol. This is an open-label study and the patients and surgeons are informed of the randomization outcome. Outcome analyses are also performed without blinding. Randomization is carried out as follows: 120 sheets of paper stating either “Single Anastomosis Gastric Bypass” or “Roux-en-Y Gastric Bypass” are divided into groups of four and six containing equal numbers of both outcomes and then sealed into opaque envelopes. These groups of opaque envelopes are distributed to both centers (80 envelopes for HUH and 40 envelopes for OUH) and then divided into two batches (for patients with diabetes and those without). The goal of this allocation sequence is to have equal numbers of patients in both groups at both centers and also an equal number of patients with diabetes in both groups at both centers.

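### Surgeons who recruit also randomize, unblinded, from balanced envelope groups of four and six, so one who tracks past allocations can guess the next arm about 69% of the time

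*Protocol article*

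**What the plan says.** All of the scheme is in the protocol article under Study sites and randomization.

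- **Who randomizes:** "Surgeons performing the intervention recruit eligible patients at a preoperative visit (study baseline) and randomize them according to protocol".
- **Masking:** "This is an open-label study and the patients and surgeons are informed of the randomization outcome".
- **Blocks:** the sheets are "divided into groups of four and six containing equal numbers of both outcomes and then sealed into opaque envelopes".
- **Strata:** "80 envelopes for HUH and 40 envelopes for OUH) and then divided into two batches (for patients with diabetes and those without". This gives four centre-by-diabetes strata. The batch sizes are not stated.
- **Totals:** the scheme starts from "120 sheets of paper stating either" one or the other operation. Under Sample size, "we decided to recruit 60 patients for both treatment groups", which is also 120.
- **Aim:** equal arms at each centre, and equal numbers of patients with diabetes in both arms at each centre.

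Three other places matter. Exclusion criteria include any further condition that the investigator judges hazardous or likely to disturb the study. Interim results report 60 patients randomized, 13 and 11 of them with type 2 diabetes. Trial status expects recruitment to run to November 2019.

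**The concern.** Concealment needs more than an envelope that cannot be read through. When the person who selects the patient knows every earlier allocation in the stratum, and the sequence returns to balance every four or six patients, past allocations give information about the next one. A recruiter with a view on which operation suits a given patient could then enrol, defer or exclude on the strength of a guess. The open-ended exclusion criterion would cover such a decision.

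The Conclusion section says both centres are more experienced with RYGB, so a preference is conceivable. Selection on unmeasured prognosis cannot be removed by the adjusted models under Statistical analyses, and outcome analyses are unblinded as well.

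A lesser concern is supply. Envelopes equal in number to the patients, divided in advance by diabetes, suffice only if each centre's diabetes count happens to equal its batch size.

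**Working it through.** **Inputs.** Block sizes 4 and 6 balanced 1:1, and envelopes 80 + 40 = 120 (Study sites and randomization); enrolment 60 + 60 = 120 (Sample size); diabetes share (13 + 11)/60 = 40% (Interim results). Assumptions: the 40% share holds at both centres, patients arrive independently, and the recruiter knows the full stratum history. The plan gives no figure for predictability or envelope supply, so there is none to reproduce.

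**1. Guessing the arm that is behind.** Every block ends in balance, so this strategy needs no knowledge of block sizes. The chance of a correct guess, position by position, is:

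- Block of four: 1/2 + 2/3 + 2/3 + 1 = 2.833, and 2.833/4 = 70.8%.
- Block of six: 0.5 + 0.6 + 0.6 + 0.7 + 0.7 + 1 = 4.1, and 4.1/6 = 68.3%.
- Equal numbers of each: (2.833 + 4.1)/10 = 69.3%, against 50% by chance.

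**2. Certain allocations when block boundaries are known.** In a block of 2m, the expected number of forced allocations at the end is 2m/(m + 1).

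- Block of four: 4/3, or 33%.
- Block of six: 6/4 = 1.5, or 25%.
- Equal numbers of each: (1.333 + 1.5)/10 = 28%, about 34 of 120.

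**3. Only the sizes known, not their order.** This was simulated with a guesser who updates on each allocation, each size being equally likely, for strata of 16 to 48 patients. About 6% of allocations are certain, 45–48% can be called with at least 75% probability, and the best guess is right about 69% of the time.

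**4. Envelope supply.** Let X be the number with diabetes at a centre, X ~ Binomial(N, 0.40), and k its diabetes batch. Neither batch runs short only if X = k, and |X − k| patients arrive to an empty batch.

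| Split | P(X = k), HUH | P(X = k), OUH | P(at least one batch empties) | Mean patients without an envelope |
|---|---|---|---|---|
| Best (32/48 and 16/24) | 0.091 | 0.128 | 1 − 0.091 × 0.128 = 98.8% | 3.5 + 2.5 ≈ 6 |
| Even (40/40 and 20/20) | 0.017 | 0.055 | 1 − 0.017 × 0.055 = 99.9% | 8.1 + 4.3 ≈ 12 |

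With the best split for each share, the probability is 98.3–98.9% for diabetes shares from 20% to 50%. The first patient without an envelope is, at the median, number 76 of 80 at HUH and 37 of 40 at OUH under the best split, and number 68 and 34 under the even split.

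**The case against.** **On predictability.** The plan has real safeguards: sealed opaque envelopes, two block sizes, and an eligibility work-up by an endocrinologist, surgeon, dietitian and anesthesiologist, which limits any one surgeon's discretion. The 69% assumes that the recruiter follows the whole stratum; several surgeons who do not share the history would foresee less. The 28% needs known boundaries. All of this stands as a limit on size. None of it removes the point, because neither sealing nor mixing two sizes defeats guessing the arm that is behind.

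**On condensation.** A journal article may omit who prepared, held and opened the envelopes, the batch sizes and any rule for an empty batch. That is fair, and no omission is counted here. The point rests on what the article does state: who randomizes, what they know, and the block sizes. A reader might infer that surgeons open the envelopes themselves. The text says only that they randomize.

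**On supply.** A reader might infer that a stratum runs out early and that the diabetes balance then fails. The documents do not support that. No batch size is given; with a sensible split the shortage falls among the last few patients at each centre. Moving a whole unopened group keeps the blocking intact. Moving the rest of a part-used group changes a stratum's arm difference by at most 3. If all envelopes are used, the centres still finish 40:40 and 20:20. New blocks could also be prepared.

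**On evidence of harm.** A reader might infer that selection has already occurred. The interim figures give no such sign: 30 per arm, diabetes 13 against 11, women 20 against 21, median BMI 44.0 against 44.9. Median diabetes duration differs (3 against 7 years), but in only 24 patients. These figures do not exclude bias either.

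**Conclusion.** The point holds as a weakness of allocation concealment. Open-label recruiters who randomize from strata with balanced groups of four and six can guess the next arm about 69% of the time if they track the stratum. The share they can know for certain is much smaller: about 6% if they know only the sizes, and about 28% if they know the boundaries. The 69% rests on full knowledge of the history, and the 28% and the mixed rate on equal numbers of the two sizes. This is an opportunity for selection, not evidence of it.

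The supply point is secondary. That some batch empties before its centre's quota is about 99% probable, but only about 6 patients (good split) to 12 (even split) of 120 are affected, and the harm to balance is small if whole unopened groups are moved. These figures rest on the interim diabetes share.

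**What to change.** For the patients still to be randomized (60 of 120 at the interim), as a cheap improvement:

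1. Have someone already on the study who neither recruits nor operates prepare and hold new whole blocks for each of the four strata, with surplus. Sizes should vary at random, include some larger than six, and not be disclosed.
2. Release each allocation only after the patient's eligibility, consent and diabetes stratum are irrevocably registered. A telephone call to that person is enough.
3. Do not move part-used groups between batches.

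Step 2 alone would not stop a recruiter guessing before registration, so step 1 is needed too. Larger blocks reduce guessing but do not abolish it. The expected number of correct guesses in a block of 2m is m + ½(4^m / C(2m, m) − 1). For a block of eight this is 4 + ½(256/70 − 1) = 5.33, or 67%; for ten it is 5 + ½(1024/252 − 1) = 6.53, or 65%. Forced allocations with known boundaries, 1/(m + 1), fall to 20% and 17%, and undisclosed, varied sizes make those boundaries harder to infer.

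The cost is a set of extra envelopes, some of one team member's time and a short amendment. The downsides are a change of procedure during recruitment and the loss of guaranteed exact balance: stopping inside a block can leave a small arm difference within a stratum or centre.

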**Fig. 1 Fig1:**
[figure not shown]
Trial schedule. DEXA dual-energy x-ray absorptiometry, ECG electrocardiogram, LA Los Angeles (classification), MRI magnetic resonance imaging, SAGB single-anastomosis gastric bypass, V visit

### Interventions

When our current randomized study was designed there was no consensus regarding the name for the OAGB procedure in the bariatric surgery community. Hence, we then decided to use the name SAGB and we named the trial RYSA (Roux-en-Y Gastric Bypass vs Single-Anastomosis Gastric Bypass).

#### Roux-en-Y gastric bypass

After insufflation with CO_2_ reaching 15 mmHg intra-abdominal pressure, a standard four-port laparoscopy with a subxiphoidal liver retractor in place is carried out. Biopsies of subcutaneous fat, the omentum and liver are taken (at HUH). At 5 cm below the gastroesophageal junction, an approximate 20- to 40-ml small pouch is created with linear staplers. The omentum is divided and an antecolic 80-cm BP limb is measured with a marked dissector and anastomosed end-to-side with a linear 45-mm stapler and the anterior defect is sutured in two layers with a braided absorbable 2–0 running suture. A 130-cm alimentary limb is measured with a marked dissector and enteroanastomosis is created with a 60-mm or 45-mm (at the HUH and OUH, respectively) linear stapler and the remaining anterior defect is sutured in one layer with a braded absorbable 2–0 running suture. The ends of both anastomotic staple lines are secured with an extra stich. The connection between the anastomoses is divided with two linear staplers and a biopsy of the small bowel is obtained between the staple lines (at HUH). The mesenteric defect and Petersen’s space are closed with titanium clips or a slowly (180 days) absorbable barbed running suture (at the HUH and OUH, respectively) (Fig. 2).

**Fig. 2 Fig2:**
[figure not shown]
Illustration of the Roux-en-Y gastric bypass technique

#### One-anastomosis gastric bypass

After insufflation with CO_2_ reaching 15 mmHg intra-abdominal pressure, a standard four-port laparoscopy with a subxiphoidal liver retractor in place is carried out. Biopsies of subcutaneous fat, the omentum and liver are taken (at HUH). A long gastric pouch is created with linear staplers starting horizontally at the crow’s foot and continuing towards the angle of this along a 38-Fr bougie. An antecolic 210-cm BP limb is measured with a marked dissector and anastomosed with a linear 45-mm stapler side-to-side with the distal end of the pouch. The remaining defect is sutured in two layers with a braided absorbable 2–0 running suture beginning and ending 2 cm proximal to the stapled anastomosis, thus securing the BP limb’s position parallel to the pouch (Fig. 3).

**Fig. 3 Fig3:**
[figure not shown]
Illustration of the one-anastomosis gastric bypass technique

We chose to do a 210-cm BP limb in OAGB and 80-cm (BP) and 130-cm (alimentary) limbs in RYGB to obtain equally long bypassed intestine in both groups.

### Inpatient follow-up

After the operation all patients are monitored for 2 h in the operation unit and then transferred to the ward, where blood pressure, pulse, heart rate, temperature, and blood glucose are measured and documented together with pain, nausea and fluid intake. Patients are mobilized and fluids are given as soon as possible. Patients are discharged on the first or second postoperative day if there are no abnormal symptoms or suspicion of complications (elevated heart rate, fever, pain, nausea, vomiting, low hemoglobin). Fluid intake must be at least 1000 ml/day and the patient must be sufficiently mobilized and feel fit to go home. All patients are prescribed multivitamins (Multivita Plus®) once a day, calcium carbonate and vitamin D 1000 mg + 20 IU/day, and vitamin B12 1 mg/day. Women of fertile age are also prescribed iron substitution 100 mg/day. Other prescriptions include a proton-pump inhibitor (pantoprazole 40 mg/day) for 3 months (at HUH) and the antithrombotic agent enoxaparin 40 mg/day subcutaneously for 10 days. Paracetamol 1000 mg three times a day, metamizole + pitofenone 500/5 mg three times a day and tramadol 50 mg three times a day are prescribed for pain.

### Preoperative work-up and outpatient follow-up

#### Helsinki University Hospital and Oulu University Hospital

At 8 weeks prior to the operation (the baseline of the study), all patients are evaluated for eligibility for surgical treatment according to the Finnish guidelines for management of obesity and local protocols by an endocrinologist, surgeon, dietitian and anesthesiologist. This includes a thorough medical check-up with laboratory tests, BIA, assessment of obstructive sleep apnea and a gastroscopy. If the inclusion criteria are met and no exclusion criteria are found, patients can be recruited to this study. Written consent is received for all study patients. Together with extensive blood tests, we perform an OGTT to identify patients with impaired glucose tolerance or T2DM. Preoperatively, all patients also fill in questionnaires to assess diseases, medications, lifestyle and quality of life.

At 1 month after the operation, postoperative recovery and comorbidities are assessed together with blood tests and BIA.

At 3 months all patients meet with an internist or endocrinologist, and nutritional, metabolic and safety laboratory tests are evaluated and medications for comorbidities are reviewed and optimized (at HUH). At OUH, laboratory tests are analyzed, and patients are contacted via telephone.

At 6 months a gastroscopy with comprehensive biopsies of the gastric tube, gastroesophageal junction and esophagus as well as a radioisotope scanning for the detection of bile reflux are performed (for the OAGB group at HUH).

At 6 months,12 months, 24 months, 5 years and 10 years BIA measurement and OGTT are repeated according to the same protocol as prior to the operation. Accordingly, nutritional, metabolic and safety laboratory tests are again performed. All patients also fill in questionnaires and food diaries (at HUH). At OUH, all patients meet an endocrinologist, and nutritional, metabolic and safety laboratory tests are evaluated and medications for comorbidities are reviewed and optimized.

#### University of Helsinki Obesity Research Unit

At 8 weeks before the operation, metabolic examinations and a meal tolerance test are performed for all patients at HUH. CGM is performed using the Abbott Freestyle Libre device. Biopsies of subcutaneous fat, skin and a muscle tissue (vastus lateralis muscle) are taken under local anesthesia. Blood and diurnal urinary samples are collected in order to analyze indicators of nutritional status, metabolic and safety parameters, glucose tolerance, cortisol and other hormone metabolism, bile acid metabolism, calcium homeostasis and a tendency for urolithiasis. Salivary bilirubin and microbiota and gut microbiota are analyzed from saliva and feces samples, respectively. Omics analyses are performed from blood and tissue specimens and mitochondria-specific measurements taken from tissue biopsies. DEXA and abdominal MRI and MRS are used for analysis of the distribution of fat tissue. The participants also fill out questionnaires and diaries, and they are interviewed on health, symptoms, lifestyle, and quality of life.

The exact same protocol is repeated for all patients at HUH at 6 and 12 months after the operation.

### Body composition studies

Each participant’s weight, height, and waist and hip circumference are measured and BMI and waist to hip ratio are calculated. Body composition is analyzed by BIA, DEXA, MRI, and proton MRS.

#### Bioelectrical impedance

The body water, body fat and amount of lean tissue are calculated by measuring electrical impedance (Tanita MC-980).

#### DEXA

The bone mineral content, fat mass, and fat-free mass are determined using a Lunar Prodigy whole-body scanner (GE Medical Systems, Madison, WI).

#### MRI and MRS

Body fat distribution and liver fat content are analyzed using MRI and MRS. The imaging and data analysis procedures have been described elsewhere [14].

### Indirect calorimetry

Indirect calorimetry (Cosmed Q-NRG) is used to estimate the basal metabolic rate from measurements of O_2_ consumption and CO_2_ production. This is measured with the patient lying supine in bed and breathing calmly and regularly in the canopy with a constant air flow (to be adjusted to give O_2_ and CO_2_ concentrations within the workable range).

### Fasting blood samples

Routine laboratory tests, including a complete blood count, and levels of vitamins, potassium, sodium, copper, selenium, zinc, magnesium, calcium, lactate, creatine kinase, pyruvate, creatinine, glycated hemoglobin A1c, cholesterol, low-density lipoprotein cholesterol, high-density lipoprotein cholesterol and triglycerides, plus a measure of thyroid function (with thyroid-stimulating hormone), liver enzymes (aspartate aminotransferase, alanine transferase, γ-glutamyltransferase, alkaline phosphatase, bilirubin), and synthesis markers of the liver (thromboplastin time, albumin) are taken. Lipoprotein fractions are separated for measurement of chylomicrons, high-density lipoprotein and low-density lipoprotein subspecies. In addition, metabolic markers such as cytokines (e.g., high-sensitivity C-reactive protein), systemic global metabolites (metabolomics, lipidomics, proteomics) and bile acids are analyzed. Investigation of hemostasis activity, coagulation parameters, platelet activity and function, as well as thrombin formation capacity in platelet-free and platelet-rich plasma are performed. Markers of chronic stress (e.g., copeptin, cortisol, cortisol metabolites, aldosterone, renin, metanephrine, normetanephrine) and calcium homeostasis (e.g., urate, phosphorus, intact parathyroid hormone) are also measured.

### MMT and OGTT

A mixed meal test (MMT) and OGTT are performed after an overnight (10-h) fast. During the MMT the patients eat a caloric-rich, partially liquid meal of 2620 kJ with a balanced distribution of fat (24 g), carbohydrates (76 g) and protein (24 g) (Resource® 2.5 Compact, Nestle Health Science). A fasting blood sample is collected before ingestion of the meal, and postmeal samples are collected at 15, 30, 60, 120, 180, 240 and 360 min for measurement of glucose, insulin, c-peptide, incretins, lipids and lipoproteins, appetite-regulating hormones and metabolites.

Additionally, a standard OGTT is performed with similar measurements as in the MMT. A fasting blood sample is collected after which patients take a 75-g oral glucose dose. Postglucose time points for sample collection are 0, 30, 60, 120, and 180 min.

### Saliva, urine and fecal samples

Saliva is collected after stimulation by chewing parafilm. Saliva samples are used for microbiota and metabolomics analyses.

Urine is collected for 24 h in free-living conditions at home. Urine samples are used to measure urinary albumin, urea, creatinine, sodium, potassium and magnesium, and for metabolomics analyses. Markers of chronic stress (e.g., cortisol, cortisol metabolites, aldosterone, adrenalin metabolites) and calcium homeostasis (e.g., calcium, citrate, urate, oxalate, phosphorus) are measured. Furthermore, an additional urine sample is collected on a study morning to perform a pregnancy test for females of childbearing age.

Feces are collected either at the study center or at home and stored at –80 °C within 24 h. Feces samples are used for metagenome sequencing and fecal metabolites, including fatty acid composition.

### Fat, muscle and skin biopsy

A subcutaneous fat biopsy by liposuction (approximately 3 g) is taken under local anesthesia from the abdominal area. One part of the sample is immediately frozen and stored in liquid nitrogen or −80 °C until used for transcriptional, protein or other biochemical analyses, and another part is further prepared for isolation of adipocytes and stroma vascular fraction (SVF) cells. Fat cell size is determined from fresh adipocytes. Part of the SVF is prepared for cell culture. Fat is also stored in paraffin for future immunohistochemical analysis.

A needle muscle biopsy (~50 mg) is taken under local anesthesia and sterile conditions from the vastus lateralis muscle with a Bergström needle. Part of the sample is immediately frozen in liquid nitrogen after excision and stored at –80 °C until used for transcriptional, protein or other biochemical analyses. Other parts are prepared for histological staining and electron microscopy and for myoblast culture.

A skin biopsy (approximately 1 × 1 cm) is taken from the abdomen before the fat biopsy. The biopsy specimen is processed for a fibroblast culture.

Using the adipose tissue and muscle biopsies, and also from the isolated SVF and myoblast cells, we perform a comprehensive set of analyses measuring mitochondrial biogenesis and function.

